### Primary outcome measure

The primary outcome measure is 'treatment response' measured at 24 week outcome data collection. 'Treatment response' will be defined as a reduction of 50% or more in the patient's baseline SCL-20D score. A binary primary outcome was chosen as this is a pragmatic trial and an outcome of clear clinical relevance is therefore required.

### Secondary outcome measures

The following secondary outcome measures will be assessed:

• Remission of major depressive disorder, defined as an SCL-20D score of < 0.75 at 24 and 36 and 48 weeks (higher than in primary care trials, to allow for cancer-related somatic symptoms).

• Depression severity, defined for each patient as the average of their SCL-20D score at 24, 36 and 48 weeks.

• Patient's self-rated improvement of depression, measured by a five point global improvement scale.

### Tertiary outcome measures

The following tertiary outcome measures will be assessed at 12, 24, 36, and 48 weeks from randomisation:

• Severity of depression symptoms, measured by the SCL-20D.

• Remission of major depressive disorder, defined as an SCL-20D score of < 0.75.

• Remission of major depressive disorder, defined as an SCL-20D score of < 0.5.

• Severity of anxiety symptoms, measured by the SCL-10A.

• Severity of pain and fatigue, measured by the relevant symptom scales of the EORTC QLQ-C30.

• Physical, social and role functioning, and overall health and quality of life measured by the relevant scales of the EORTC QLQ-C30.

• Patient's satisfaction with care, measured by a 5-point Likert scale item developed specifically for the trial.

### Measures of cost and health-related quality of life

The following economic outcome measures will be assessed at 12, 24, 36 and 48 weeks from randomisation:

• Cost of 'usual care' treatments received for depression.

• Cost of health care service use (primary, secondary and community based).

• Cost of the trial intervention.

• Health related quality of life, measured by EQ-5D.

### Data collection

Baseline data will be obtained by the assessor at the end of the face-to-face eligibility assessment as near as possible prior to randomisation

Outcome data collection will be obtained by a dedicated team who are blind to group allocation and are situated and managed independently from the trial team. This team will be managed by the Scottish Mental Health Research Network (SMHRN). Outcome data will be collected at 12, 24, 36 and 48 weeks from randomisation.

All baseline and outcome data will be collected using self-report questionnaires sent by mail with telephone calls or face-to-face interviews to collect missing items or whole questionnaires in order to maximise response rate. The date of completion of all questionnaires will be noted. Data collection will aim to be within one week either side of the specified follow-up date.

### Data collection instruments

The following data will be collected from patients at baseline, 12, 24, 36 and 48 weeks

• Symptom Checklist Depression Scale (SCL-20D)

• Symptom Checklist Anxiety Scale (SCL-10A)

• European Organisation for Research and Treatment of Cancer Quality of Life Questionnaire (EORTC-QLQ-C30)

• Patient's satisfaction with depression care (question developed specifically for the trial)

• EuroQol-5D (EQ-5D)

• Treatments received for depression (measures developed specifically for the trial)

• Use of health care services (measures developed specifically for the trial)

At baseline, demographic details and information about the patient's cancer will also be collected.

### Sample size

The power calculation is based on the primary outcome measure, namely 'treatment response' defined as a reduction of 50% or more in baseline SCL-20D score at 24 weeks. Two treatment groups of 240 patients (i.e. 480 in total) will give 90% power to detect an increase in the response rate from 35% to 50% at the 5% significance level, and 80% power to detect an increase in the response rate from 35% to 48% at the 5% significance level. Targeting recruitment at a total of 500 patients allows for a 4% loss to follow up at six months. This loss to follow-up rate is comparable with that achieved in the recently completed efficacy trial.

### Method of randomisation

In order to ensure similarity in the baseline characteristics of the two treatment groups, randomisation will be carried out using a combination of stratification and minimisation. Stratification will be by trial centre (Edinburgh, Glasgow) and minimisation variables will be age (≤50, 51–60, >60), cancer type (breast, genito-urinary, gynaecological, other) and sex. The minimisation variables are all equally weighted and will be balanced within each centre according to a deterministic algorithm. When the two treatment arms are perfectly balanced in terms of the age, cancer type and gender characteristics of a new subject, treatment allocation will occur randomly with equal probability assigned to the two treatments. The randomisation system is maintained by the Division of Clinical Neuroscience (DCN) Clinical Trials Unit at the University of Edinburgh, and allows for the real-time randomisation of patients using either a telephone (IVR) or web-based user interface.

### Statistical analyses

A single main analysis will be performed at the end of the trial when all outcome data have been collected. An independent Data Monitoring Committee will review confidential interim analyses of accumulating data at least annually. A detailed Statistical Analysis Plan will be developed prior to closure of the trial database and prior to the unblinding of the treatment allocations. The main analyses will be performed blind to treatment allocation on the 'intention-to-treat' principle, incorporating all randomised patients with usable outcome data.

The primary outcome measure of treatment response at 24 weeks will be analysed using logistic regression, with the minimisation variables being included as covariates. The results will be reported as an adjusted odds ratio with its corresponding 95% confidence interval.

The secondary outcome measure of remission of major depressive disorder at each and all of 24, 36 and 48 weeks will be analysed in the same way as the primary outcome measure.

The secondary outcome measure of depression severity averaged over 24, 36 and 48 weeks will be analysed using analysis of covariance, with the baseline SCL-20D score and the minimisation variables being included as covariates. The results will be reported as an adjusted mean difference in SCL-20D score with its corresponding 95% confidence interval.

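### Allocation is stratified by centre, but the three specified models adjust only for the minimisation variables, so centre is omitted as written: a small, conservative mismatch that is free to correct

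*Protocol article*

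**What the plan says.** The Method of randomisation section names two kinds of allocation factor. Centre is the stratification factor and the others are minimised: "Stratification will be by trial centre (Edinburgh, Glasgow) and minimisation variables will be age" in three bands, followed by "cancer type (breast, genito-urinary, gynaecological, other) and sex". The two kinds are not interchangeable, because minimisation operates inside each centre: "The minimisation variables are all equally weighted and will be balanced within each centre according to a deterministic algorithm".

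The Statistical analyses section fixes the covariates of three models:

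- **Treatment response at 24 weeks (primary):** it "will be analysed using logistic regression, with the minimisation variables being included as covariates", reported as an adjusted odds ratio.
- **Remission at 24, 36 and 48 weeks:** this "will be analysed in the same way as the primary outcome measure".
- **SCL-20D averaged over 24, 36 and 48 weeks:** analysis of covariance "with the baseline SCL-20D score and the minimisation variables being included as covariates".

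Centre is named in none of them. The article gives no model for self-rated improvement or for the tertiary outcomes, so the point cannot be extended to those.

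**The concern.** Of the four factors used to allocate patients, three are in the models and one is not, and no reason is given for treating centre differently. Stratifying on a factor removes chance imbalance in it between the arms. If that factor predicts outcome, the treatment estimate varies less from trial to trial than an analysis that ignores the factor assumes. The test is then conservative and some power is given away.

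Centre could matter here. The clinics belong to two NHS organisations, Care Managers are drawn from site-specific lists, and usual care is whatever each patient's GP and oncologist provide. None of this shows that response differs between centres, and the article gives no centre effect.

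This is not a detail left for the SAP. The article names a covariate set, and that set does not match its own randomisation scheme.

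**Working it through.** **1. The plan's own figure.** Inputs from the Sample size section: 240 per arm, for "90% power to detect an increase in the response rate from 35% to 50% at the 5% significance level". A second pair in the same section is 35% versus 48% with 80% power. Two-sided testing is assumed. The two-proportion formula is

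n = [1.96·√(2·p̄(1−p̄)) + z_power·√(p₁(1−p₁)+p₂(1−p₂))]² / (p₂−p₁)²,

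and with continuity correction n_c = (n/4)·[1 + √(1 + 4/(n·|p₂−p₁|))]².

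| Rates | Power | Without correction | With correction |
|---|---|---|---|
| 35% vs 50% | 90% | 227 per arm | 240 per arm |
| 35% vs 48% | 80% | 225 per arm | 240 per arm |

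Allowing for 4% loss, 480/0.96 = 500. The stated sample size is reproduced and does not depend on whether centre is in the model. Without the continuity correction, 240 per arm gives 91.6% power at 35% versus 50%, which is the natural baseline for the simulations below.

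**2. Hand check of the test's size.** Assume two equal centres, exact 1:1 balance within each, and an overall response of 35% under the null. The variance assumed without centre is proportional to 0.35 × 0.65 = 0.2275. The true variance is proportional to the mean within-centre variance.

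| Response in the two centres | Centre odds ratio | Within-centre variance | Ratio to 0.2275 | Type I error, 2Φ(−1.96/√ratio) |
|---|---|---|---|---|
| 30%, 40% | 1.56 | (0.21+0.24)/2 = 0.2250 | 0.989 | 4.9% |
| 25%, 45% | 2.45 | (0.1875+0.2475)/2 = 0.2175 | 0.956 | 4.5% |
| 20%, 50% | 4.00 | (0.16+0.25)/2 = 0.2050 | 0.901 | 3.9% |

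**3. Simulation over assumed centre odds ratios.** 480 patients, two equal centres, 1:1 within centre, overall rates held at 35% versus 50%, Wald test at two-sided 5%, 8,000 trials per row. Entries are without / with centre in the model.

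| Centre odds ratio | Type I error | Power | Mean treatment odds ratio |
|---|---|---|---|
| 1.5 | 4.9% / 5.0% | 91.8% / 92.0% | 1.87 / 1.88 |
| 2 | 5.0% / 5.3% | 91.3% / 92.2% | 1.86 / 1.90 |
| 3 | 4.2% / 5.1% | 92.3% / 93.5% | 1.86 / 1.95 |
| 4 | 4.2% / 5.3% | 92.1% / 93.6% | 1.86 / 2.01 |

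The Monte Carlo standard error of a 5% rejection rate is √(0.05 × 0.95/8000) = 0.24 points, so differences of a few tenths in the type I error column are noise.

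**4. Simulation by control response in each centre.** 120 per arm per centre, overall 35% versus 50%.

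- 25% and 45%: type I error 4.7% without centre, 5.1% with it; power 91.3% and 92.5%. A repeat of the power run with 20,000 trials gave 91.7% and 92.8%.
- 20% and 50%: type I error 4.0% and 5.2%; power 92.5% and 94.3%, a difference of 1.8 points, or at most 1.9 allowing for rounding.
- 30% and 40%: a power difference of 0.3 points.

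**5. Why the odds ratio moves.** Take control rates of 20% and 50% and a treatment odds ratio of exactly 2 in each centre. Treated odds are 0.25 × 2 = 0.5 and 1 × 2 = 2, so treated rates are 33.3% and 66.7%. Overall this is 35% versus 50%, whose odds ratio is (0.50/0.50)/(0.35/0.65) = 1.857. Both numbers are correct. One is averaged over centres and the other is conditional on centre.

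Age, cancer type and sex were not simulated. The ANCOVA was not simulated either, because the article gives no standard deviation for SCL-20D.

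**The case against.** **It may be only wording.** The article describes a single combined scheme, and its authors may have used the term minimisation variables as shorthand for every allocation factor. Centre is never expressly excluded, and a detailed SAP is promised before unblinding. This is possible, and it limits what can be claimed about the analysis finally run. It does not remove the mismatch: the randomisation section defines the term without centre, and a statistician following the text would leave centre out.

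**Stronger readings that the documents do not support:**

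- *Power falls below plan.* A reader who fixes the within-centre odds ratio at 1.857 would find 88.7% power without centre at control rates of 25% and 45%, and 85.8% at 20% and 50%. That setting shrinks the effect. At 20% and 50%, the treated odds are 0.25 × 1.857 = 0.464 and 1.857, so the treated rates average (31.7% + 65.0%)/2 = 48.4%, not the 50% planned. Power with centre is then only 88.5%, so most of the fall is not due to omitting centre. At the planned overall rates, power without centre stays above 90%.
- *Adjusting for centre would shrink the reported standard error.* In logistic regression it does the opposite: the mean standard error of the log odds ratio rises from 0.188 to 0.193 (25% and 45%) or 0.200 (20% and 50%). Power improves because the conditional log odds ratio rises by more. The usual precision argument applies to the ANCOVA, for which no figure can be given.
- *The odds ratio without centre is biased towards 1.* The shift is non-collapsibility, a change in the quantity estimated. The sample size calculation itself uses overall rates.
- *False positives increase.* With balance within centre, the error is in the conservative direction.

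**The size depends on an undocumented centre gap.** This stands. Both centres share eligibility criteria, screening service and treatment manual, and a between-centre odds ratio of 4 would be large.

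**Conclusion.** The mismatch is real on the face of the text and its consequence is small. As written, the response, remission and average-severity models omit the factor on which allocation was stratified. For the primary logistic analysis, over assumed centre odds ratios of 1.5 to 4, the model without centre has type I error of about 4.0% to 5.0% and gives up about 0.2 to 1.9 points of power at 35% versus 50%, with power remaining above 90%. For a small gap such as 30% and 40% the loss is negligible. The result rests on equal centres, exact balance within centre and an assumed centre effect.

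Nothing here threatens the validity of the trial's conclusion or its sample size. It is worth correcting because the correction is free, and because adding centre after the event would be a departure from the published primary model.

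**What to change.** In the Statistical analyses section, and in the SAP before treatment allocations are unblinded, define the covariates of the response, remission and average SCL-20D models as trial centre (the stratification factor) together with the minimisation variables age, cancer type and sex. The ANCOVA keeps baseline SCL-20D in addition. State that the adjusted odds ratio is then conditional on centre as well as on the minimisation variables.

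The cost is one sentence and, with two centres, one degree of freedom per model. Centre is already recorded at randomisation, so no new data are needed, and the target stays at 240 per arm and 500 in total.

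### The logistic models for remission and response omit baseline SCL-20D, which the severity ANCOVA includes: valid, but less efficient than it could be for remission

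*Protocol article*

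**What the plan says.** All references are to the protocol article.

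- **Primary outcome.** Response is a fall of at least half from the patient's own baseline SCL-20D at 24 weeks (Primary outcome measure). It "will be analysed using logistic regression, with the minimisation variables being included as covariates" (Statistical analyses).
- **Secondary outcome, remission.** "Remission of major depressive disorder, defined as an SCL-20D score of < 0.75 at 24 and 36 and 48 weeks" (Secondary outcome measures). It "at each and all of 24, 36 and 48 weeks will be analysed in the same way as the primary outcome measure" (Statistical analyses), so it takes the same covariates.
- **Secondary outcome, severity.** The average SCL-20D over 24, 36 and 48 weeks goes into an ANCOVA "with the baseline SCL-20D score and the minimisation variables being included as covariates" (Statistical analyses).
- **What the allocation balances.** Stratification is by centre, and the "minimisation variables will be age (≤50, 51–60, >60), cancer type (breast, genito-urinary, gynaecological, other) and sex" (Method of randomisation). Baseline SCL-20D is not among them.
- **Availability.** SCL-20D heads the list of instruments under "The following data will be collected from patients at baseline, 12, 24, 36 and 48 weeks" (Data collection instruments).

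The Statistical analyses section adds that a detailed SAP will be written before database closure and unblinding.

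**The concern.** Remission and severity use the same scale, the same patients and the same three time points. One is adjusted for the baseline value and the other is not, and the article gives no reason. The two results could differ partly because their covariate sets differ.

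Remission is the more exposed of the two binary outcomes. It is a fixed cut-off on the scale measured at entry, so if baseline and follow-up scores are correlated, patients who start lower reach it more easily. Eligibility sets no minimum SCL-20D: entry is by DSM-IV diagnosis after a HADS screen. Distance from 0.75 at entry is therefore uncontrolled. The power calculation covers only response, so nothing in the article secures power for remission.

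At stake is some power for a secondary outcome, and some sensitivity of its estimate to a chance difference in baseline severity between arms.

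**Working it through.** **1. The plan's own sample size.** Inputs from Sample size: 240 per arm, 35% v 50% with 90% power, 35% v 48% with 80% power, 5% level (two-sided assumed).

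n = [1.960·√(2p̄(1−p̄)) + z·√(p₁(1−p₁) + p₂(1−p₂))]² / (p₂−p₁)²; with continuity correction, n′ = (n/4)·[1 + √(1 + 4/(n(p₂−p₁)))]².

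- 35% v 50%: (1.960×0.6991 + 1.282×0.6910)² / 0.15² = 226.2, so 227. Corrected: (226.2/4)(1 + 1.0573)² = 239.3, so 240.
- 35% v 48%: (1.960×0.6968 + 0.842×0.6907)² / 0.13² = 224.3, so 225. Corrected: (224.3/4)(1 + 1.0664)² = 239.5, so 240.
- 480/0.96 = 500.

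The stated figures reproduce with the continuity-corrected, unadjusted formula. They do not rely on any covariate.

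**2. Power with and without baseline.** The article gives no SCL-20D means, SDs or correlations, so these are assumed: baseline mean 2.0 or 2.3, baseline SD 0.6, follow-up SD 0.8, correlation 0.2 to 0.6. Each outcome was calibrated to 35% v 48%. There were 480 patients per trial and 2,000 trials per cell. Logistic regression was fitted with treatment alone and with treatment plus baseline; the minimisation variables were left out of both. Remission was simulated at one time point. Entries are power in %, without → with baseline.

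| Correlation | Remission, mean 2.0 | Remission, mean 2.3 | Response, mean 2.0 | Response, mean 2.3 |
|---|---|---|---|---|
| 0.2 | 83.6 → 84.6 | 80.9 → 82.1 | 81.5 → 82.4 | 79.7 → 81.6 |
| 0.3 | 83.9 → 87.0 | 83.4 → 85.8 | 82.3 → 82.8 | 83.7 → 84.0 |
| 0.4 | 80.8 → 85.3 | 82.2 → 86.2 | 82.4 → 82.5 | 83.1 → 83.3 |
| 0.5 | 82.4 → 88.0 | 84.8 → 89.5 | 82.0 → 83.0 | 82.6 → 83.6 |
| 0.6 | 81.6 → 91.3 | 80.5 → 90.5 | 81.4 → 84.0 | 80.8 → 82.9 |

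The remission gain is 1.0 to 1.2 points at 0.2, 2.4 to 3.1 at 0.3, 4.0 to 4.5 at 0.4, 4.7 to 5.6 at 0.5 and 9.7 to 10.0 at 0.6. The response gain is 0.1 to 2.6 points.

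**3. Other assumptions.** Two further simulations were calibrated to a response rate of 35% v 50%.

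- Follow-up SD 0.7: remission power rose by 1 to 2 points at 0.2 to 0.3, from 78.6% to 84.8% at 0.5, and from 74.5% to 84.8% at 0.6. Response gained 0.2 to 0.7 points.
- Follow-up SD 0.8: remission gained about 1 point at 0.2 to 0.3, 4 at 0.4 to 0.5 and 9 at 0.6. Response gained 0.1 to 1.7 points.

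**4. Validity.** With no treatment effect, the rejection rate in the step 2 simulation was 0.042 to 0.059 across all cells, with and without baseline. Simulation error is √(0.05×0.95/2000) ≈ 0.005.

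**5. Where the power comes from.** For remission at correlation 0.6 and baseline mean 2.0, the odds ratio moves from 1.72 to 2.04 while the standard error of its log rises from 0.188 to 0.217. The ratio of the two goes from ln 1.72/0.188 = 2.88 to ln 2.04/0.217 = 3.29. The standard error does not shrink; the conditional odds ratio lies further from 1.

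**6. Chance imbalance.** The standardised baseline difference has standard error √(2/240) = 0.091, so its 95% range is ±1.96×0.091 = ±0.18 SD. The approximate shift in the unadjusted odds ratio at that extreme is exp(0.179×|ln(baseline OR per SD)|), using the simulated baseline odds ratios.

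- Remission: OR per SD 0.72 (correlation 0.2) gives 1.06; 0.49 (0.4) gives 1.14; 0.28 (0.6) gives 1.26.
- Response: 0.95 (0.4) gives 1.01; 0.63 (0.6) gives 1.09, the largest.

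**The case against.** The strongest case against is that nothing here is an error. Adjusting binary outcomes for the minimisation variables is a legitimate pre-specified analysis, and using the baseline value only in the ANCOVA is not a contradiction. Response already has the patient's own baseline as its denominator. The remission gain depends on a correlation that the article does not give. Entry requires a HADS total of 15 or more and current major depression, which may narrow the baseline range and lower that correlation. Only single-time-point remission was simulated, whereas the plan analyses each and all of three. Adding baseline also changes the quantity estimated to a more conditional odds ratio.

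Most of this stands, and it rules out four stronger readings that a reader might infer.

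- **That the planned estimates are biased.** Chance imbalance under randomisation is sampling variation, and type I error holds without adjustment.
- **That precision is lost.** In logistic regression the standard error stays the same or rises on adjustment; the gain is in power.
- **That the primary analysis is materially weakened.** The gain there is 0 to 3 points, and close to zero at correlations of 0.3 to 0.4.
- **That the sample size is affected.** It is an unadjusted calculation and reproduces.

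Two parts of the objection do not dispose of the point. The article names the covariates for each model, so this is a stated choice and not a detail left open for the SAP. And the planned result is already an adjusted odds ratio, so adding baseline makes it more conditional without introducing a new kind of estimate.

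**Conclusion.** The point holds as one of efficiency and consistency, mainly for remission. For a single time point the power gain is about 1 to 3 points at correlations of 0.2 to 0.3 and about 4 to 10 points at 0.4 to 0.6, and no simulated cell showed a loss. Adjustment also reduces, under a linear-logit assumption, the effect of a chance baseline difference on the estimate. For response the case is mainly consistency with the ANCOVA.

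Confidence is high on what the article says and on the direction. It is moderate on size, which rests on assumed means, SDs and correlations. The gain for remission at all three visits was not calculated.

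**What to change.** In the SAP, before unblinding, add baseline SCL-20D as a continuous covariate to the logistic models for remission, alongside the minimisation variables, and to the response model for consistency with the severity ANCOVA. State that the reported odds ratios are then conditional on baseline severity as well as on the minimisation variables, and record the change from the published article.

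The cost is wording and one degree of freedom per model in about 480 patients. No new data are needed: the score is already collected, and response cannot be computed without it. The sample size stays as it is.
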